**Fig. 2 Fig2:**
[figure not shown]
Minimum sample sizes per countries

#### Intervention

Although C4D adapts the intervention features to country-specific guidelines, contexts and needs, there is an overall approach to achieve a robust, structured framework. The intervention consists of a T2DM self-management education and support group program [31], based on the I-Change model [26], and developed over 12 months, the program consists of two phases: an intensive phase followed by an aftercare intervention, each lasting 6 months.

The intensive phase provides participants with theoretical content and practical activities on the 4 pillars - nutrition, physical activity, sleep and relaxation - of RD2N best practice (Fig. 3). Activities and workshops related to this content include interpretation of changes in glucose levels throughout the day, biometric feedback, physical exercises, relaxation and coaching practices, and cooking classes. C4D provide people living with T2DM with skills for incorporating healthy habits into their lifestyles in an experiential dynamic way (i.e. participants must ‘live’ and practice the concepts they receive during the theoretical sessions). For pedagogic and organizational reasons people living with T2DM will be organized into groups of 20 people approximately.

**Fig. 3 Fig3:**
[figure not shown]
Pillars of C4D intervention

The intensive phase tests two different delivery modes with identical content, one face-to-face and the other telematic, supported by a digital platform in both cases. The face-to-face modality refers to interventions consisting of about 6 on-site group training sessions over 6 months. A novel aspect of C4D is the inclusion of an overnight stay in order to: (a) promote group bonding, through joint acquisition of the knowledge received and its practice; (b) focus attention, by taking participants out of their own environment, responsibilities and situation at home; (c) aid follow-up, as the stay would allow for greater control over program follow-up (fewer triggers in the program environment, such as e.g., snacking); (d) guarantee for safety, as participants would feel physically and emotionally safe (especially participants on hypoglycaemic medication); (e) ease the burden, as the two start days are fully scheduled and intensive. Conversely, the telematic modality refers to several fully digital group sessions. The online platform will offer support throughout the duration of both intervention modalities, including coaching, close personal advice, and physician-monitoring of medication use.

The aftercare intervention over the following 6 months ensures that barriers are removed, and new habits become sustainable over time. Integrating T2DM self-care into daily life is a challenge for participants and their families. Therefore, individual participant characteristics, social determinants of health, and psychosocial factors should be part of the person-centered care, respecting, and responding to their individual preferences and barriers [1].

#### Evaluation

C4D includes three types of evaluation: impact, process and economic evaluation.

The impact of the intervention will be assessed in terms of behavioural change, participant clinical characteristics related to people living with T2DM (anthropometric measures, biomarkers, medication use, etc.) and quality of life. Measurements will be taken at three time points: T1: baseline (prior to the beginning of the intervention); T2: between the intensive and aftercare phases (6 months); and T3: immediately after the end of the intervention (12 months). Trained staff using standardised methods will collect study variables, like laboratory and clinical measurements, and self-report questionnaires (Table 3); agreed validated questionnaires will be requested and made available when appropriate. The survey will be available in English and needs to be translated into local languages. The translation and translation-back process and contextual adaptation will be used to ensure compatibility with the original questionnaires adapting to regional characteristics.

**Table 3 Tab3:** Clinical and behavioural measurements

Measurements	Timeline			Data collection method
	T1: 0 baseline	T2: 6 months	T3: 12 months	
Sociodemographic characteristics)	x			Self-reported questionnaire
Lifestyle behaviors (smoking, diet pattern, alcohol intake)	x			Self-reported questionnaire
T2DM duration	x			Medical record
Height	x			Clinical measurement
Weight	x	x	x	Clinical measurement
Waist circumference	x	x	x	Clinical measurement
Blood pressure	x	x	x	Clinical measurement
Serum lipids	x	x	x	Laboratory test
Glycosylated hemoglobin	x	x	x	Laboratory test
Medication for diabetes	x	x	x	Medical record
Medication for blood pressure and lipids	x	x	x	Medical record
Quality of life	x	x	x	Self-reported questionnaire
Perceived health	x	x	x	Self-reported questionnaire
Self-care for chronic diseases	x	x	x	Self-reported questionnaire
Self-efficacy	x	x	x	Self-reported questionnaire
Fatigue	x	x	x	Self-reported questionnaire
Sleep problems	x	x	x	Self-reported questionnaire
Physical activity and muscle-strengthening	x	x	x	Self-reported questionnaire
Diet (food frequency questionnaire)	x	x	x	Self-reported questionnaire

The process evaluation considers the satisfaction and experience of participants and staff, using a self-reported questionnaire. The evaluating process follow the RE-AIM framework (Table 4). In addition to the quantitative parameters, qualitative data collect factors influencing participation/non-participation; elements contributing the outcomes; the barriers preventing adoption (both by care providers and participants); how was the intervention implemented; and what will be sustained, discontinued, or adapted, and why.

**Table 4 Tab4:** Components of RE-AIM framework

Component	Indicator
Reach	
*Inclusion*	Activities/procedures to attract possible participants
	Number of potential participants screened for eligibility
*Exclusion*	Number of potential participants excluded (per exclusion criterion)
*Background characteristics*	Characteristics of participants compared to non-participants or to target population
Effectiveness	
	Number of sessions/hours of intervention organized
	Number of intervention sessions/hours of intervention attended by each participant
	Attrition (%)
	Outcome measures (%) completed at each timepoint
Adoption	
	Characteristics of settings participating compared to non- participants
	Number (and %) of staff participating
	Characteristics of staff participants vs. typical staff
Implementation	
	Adaptations made to intervention (Phase 1)
	Cost of intervention
	Consistency of implementation across staff/settings
Maintenance	
	Outcome measures at 12 months
	Adaptations made to intervention (Phase 2)
	Model integration to the organization

Socio-demographic characteristics such as sex, age, education, immigrant background, cohabitation and income level will be analysed.

C4D will collect data on the costs, and the economic impact of the implemented practice, comparing the intervention costs against the benefits of the practice (e.g. quality of life measured with the validated questionnaire). Economic data collection will include the transfer and adaptation costs of the program per country and the implementation phase. Transfer and adaptation data will include developing the online platform, translating and adapting the materials, planning the practicalities of the intervention and training the trainers. The implementation costs will include labour (cost of training staff to deliver the intervention and the personnel cost of the actual intervention), capital (the cost of renting spaces to undertake practice’ activities), administrative (the cost of promoting the intervention to eligible participants), consumables (other materials, tools, goods needed for the intervention implementation) and overhead costs.

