**Methods:**

A quasi-experimental study (without a control group) will be conducted to evaluate the CARE4DIABETES program, which is based on the Reverse Diabetes 2Now best practice. The program will involve more than 120 healthcare professionals and 860 people with T2DM from 12 European countries - Belgium, Bulgaria, Finland, Hungary, Italy, Greece, Malta, Poland, Portugal, Slovakia, Slovenia and Spain. Patients will be enrolled based on clinical criteria and motivation for change. The program will have two phases, an intensive phase (6 months) with face-to-face and online training to achieve behavioral change, and an online aftercare phase (6 months) to consolidate changes. The program will be evaluated for impact, sustainability and cost-effectiveness using a combination of validated questionnaires at baseline, six months and one year after the start of the intervention.

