There is also a growing body of evidence for T2DM remission, that can be achieved through intensive behavioural interventions, alone or combined with bariatric surgery or pharmacological interventions [15–17]. T2DM remission is considered when maintaining glycated haemoglobin below 6.5% without pharmacological treatment for three months [18], and it has been recognized by the World Health Organization and scientific associations as an appropriate therapeutic goal [19]. However, according to the American College of Lifestyle Medicine, therapeutically dosed intensive lifestyle modifications should be preferentially recommended as the primary modality for T2DM care and remission [20]. Interventions should include personalized nutrition coupled with physical activity engagement as ways to reach weight loss [19]. However, long-term weight regain is the usual hurdle encountered by patients and clinicians in the real-world setting, as the difficulty of long-lasting restricted diets, such as very low-calorie or nutritional ketosis diets, hinders the sustainability of any potential results. Therefore, studies targeting different populations on the efficacy of various complementary strategies for weight management, including mental stress and sleep disorders [21], are required [19]. Additionally, the American Diabetes Association has introduced another recommendation for the inclusion of technology assisted T2DM programmes based on patients’ preferences [22].

Against this background, a multicomponent and multidisciplinary programme called “Reverse Diabetes 2Now” (RD2N) was developed in The Netherlands seeking remedy for T2DM [23]. RD2N focuses on improving participant skills -rather than just knowledge- to manage relevant components of their lifestyle, regaining control over their disease. In essence, RD2N is a 6-month programme that provides intensive group-based counselling on nutrition, physical activity, sleep and stress management, biometric feedback, and cooking classes, combined with a digital coaching platform and close physician-monitoring of medication use. In preliminary studies, RD2N has demonstrated lasting real-life benefits, especially in terms of body weight, medication use and quality of life in people living with T2DM [24].

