## Methods

### Design and ethical considerations

C4D will be a one-group pre-test/post-test quasi-experimental study, conducted in concert in 12 countries. Briefly, C4D will evaluate the acceptability and efficacy of an innovative multicomponent intervention addressing several lifestyle behaviours (i.e. nutrition, physical activity, sleep, and stress management), that can trigger the achievement of long lasting body weight control, healthy glucose levels, lowering -and in some cases interrupting- medication consumption, reducing comorbidities, complications and associated healthcare costs, and improving health-related quality of life. The intervention will be based on the “Integrated Model for explaining motivational and behavioural change” (I-CHANGE model) and will focus on improving participants’ skills - not just knowledge - to manage relevant components of their lifestyle [26]. The structured implementation process, including training and capacity building of healthcare personnel and cultural adaptation according to local situation, aims to produce a sustainable lifestyle care model that can be scaled up nationally. Each country/partner will have a local multidisciplinary team in charge of driving the process, consisting of at least a diet expert, registered nurse or general practitioner, a coach, facilitator or equivalent and a lead coordinator (Table 1). The C4D will run from February 2023 to January 2026.

**Table 1 Tab1:** Roles and functions of the intervention team by voeding Leeft foundation

Role	Responsibilities in RD2N practice	
Diet expert	• Physiological explanation of the metabolic disturbance of type 2 diabetes (insulin resistance). • Guidance for participants in changing eating habits.	
Registered Nurse or General Practitioner	• Safe process guidance for individual participants. • Individual and group guidance on reduction of medication and reversing type 2 diabetes. • Manage participant record and registration. • Contact with the lead practitioner of the participant.	
Coach/facilitator or equivalent	• Create a safe setting for the individual and the group. • Activate and monitor group dynamics. • Guidance in awareness and behavioural change. • Guide to activation and integration of sustainable behaviour.	
Coordinator	• Quality assurance. • Practical organization of the program • Communication with participants. • Administration participants and keeping overview of progress.	

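### Table 4 counts 12-month outcomes as Maintenance, but T3 falls at the end of the 12-month intervention, so persistence is observed only under aftercare and never after support stops

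*Protocol article*

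**What the plan says.** The Intervention section describes the programme as "developed over 12 months, the program consists of two phases: an intensive phase followed by an aftercare intervention, each lasting 6 months". Aftercare is thus part of the intervention and not a follow-up period after it.

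The Evaluation section states that "Measurements will be taken at three time points". T1 is baseline. The second is "T2: between the intensive and aftercare phases (6 months", and the last is "T3: immediately after the end of the intervention (12 months". Table 3 has columns for 0, 6 and 12 months and none later.

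Table 4, which sets out the RE-AIM components, places "Outcome measures at 12 months" under Maintenance. The same heading also holds two programme-level items: adaptations made in Phase 2, and integration of the model into the organisation.

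The abstract says "The program will be evaluated for impact, sustainability and cost-effectiveness", and gives as the means validated questionnaires at baseline, six months and one year from the start of the intervention.

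**The concern.** At participant level, maintenance and sustainability suggest that a change survives when the support that produced it is withdrawn. The article gives its own reason to care about this. The Introduction says that "long-term weight regain is the usual hurdle encountered by patients and clinicians in the real-world setting", and the Design section names "long lasting body weight control" among the things the intervention may bring about. Yet each post-baseline measurement is made either between the two phases or at the moment the second one ends.

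The results are meant to inform guidelines for transfer to other European health systems and to support EU policy. If 12-month outcomes appear under Maintenance without qualification, a health system could take them as evidence that effects last beyond the programme. It could then plan for a 12-month service on the belief that nothing further is needed. The limitations paragraph in the Discussion does not warn against this; it covers only the missing control group.

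**Working it through.** The check is mainly one of timing.

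**Inputs**
- Intensive phase: 6 months (Intervention section).
- Aftercare intervention: 6 months (Intervention section).
- T1, T2, T3 at 0, 6 and 12 months (Evaluation section, Table 3).
- Planning effect: 2.3 kg mean weight reduction over the first 6 months, SD 5.1 kg (Recruitment of participants).

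**Step 1. The article's own calculation, and what it covers.** For a paired t-test with 80% power and a two-sided type 1 error of 0.05 (sidedness is not stated and is assumed here), the normal approximation gives n = (SD × (1.960 + 0.842) / effect)² = (5.1 × 2.802 / 2.3)² = 38.6, that is 39. The exact noncentral t calculation needs 41, and 40 participants give 79.4% power. The stated 40 is reproduced within rounding. The 2.3 kg refers to baseline to 6 months, which is T1 to T2. The article gives no expected effect at T3 and none for any later time, so this calculation does not bear on maintenance.

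**Step 2. Time observed after all support ends.** Programme length = 6 + 6 = 12 months. Off-programme follow-up = time of T3 − programme length = 12 − 12 = 0 months.

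**Step 3. Time observed after the intensive phase ends.** T3 − T2 = 12 − 6 = 6 months. Aftercare is delivered throughout those 6 months.

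**Step 4. What each interval can answer.**

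| Interval | Support during the interval | Question it can answer |
|---|---|---|
| T1 to T2 | Intensive phase | Change during the intensive phase |
| T2 to T3 | Aftercare | Whether intensive-phase gains persist with aftercare |
| After T3 | None | Not measured |

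**Step 5. Which Maintenance and sustainability items depend on T3.** The 12-month outcome row in Table 4 does, and so does the abstract's sustainability evaluation in so far as it rests on participant questionnaires. Phase 2 adaptations, integration into the organisation, and the qualitative data on what will be continued, dropped or changed do not.

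**Step 6. Whether the data already planned allow a precise indicator.** Table 3 has 19 rows. Four are baseline only (sociodemographic characteristics; smoking, diet pattern and alcohol; diabetes duration; height). The other 15, including weight, HbA1c, medication and quality of life, are collected at T1, T2 and T3. A T2-to-T3 change is available for all 15 without any new measurement.

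**The case against.** The best reply is that the article uses Maintenance consistently in its own terms. Table 4 ties Implementation to Phase 1 adaptations and Maintenance to Phase 2 adaptations. With a two-phase programme, Phase 2 reads naturally as aftercare, whose stated role is to consolidate what was gained. The transferred best practice is itself a six-month programme, so T3 falls six months after the equivalent of its end. This stands as far as it goes: the T2-to-T3 comparison is informative about persistence. A reader might infer from the timing that the trial can say nothing about maintenance. The documents do not support that, because persistence under aftercare is measured.

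A second reply is that sustainability is partly a property of the programme. That is also right. The Design section aims at a care model that can be scaled up nationally, and the indicators for that do not need T3. What remains is that the abstract attaches sustainability to participant questionnaires ending at one year, and that the Table 4 row concerns outcome measures.

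A third reply is that the supporting phrases are background. The long-lasting weight control phrase describes what the intervention can trigger and is not an endpoint. The weight-regain sentence is linked to the difficulty of keeping to restricted diets. Both points are fair. These passages show why durability matters to the authors, but they are not themselves claims about T3.

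Finally, the article openly states when T3 occurs, and follow-up length is a design choice within a project running from February 2023 to January 2026. Nothing says that 12-month results will be reported as lasting without support. That is correct, and the absence of later follow-up is not in itself an error. The fault is that the label and the abstract leave that reading open, and nothing in the limitations closes it.

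**Conclusion.** The concern holds as a mismatch between label and data at participant level. Follow-up after support ends is 0 months, and this needs no assumption beyond the article's own dates. The Maintenance row and the questionnaire-based sustainability evaluation can support a statement about six months of persistence under aftercare, and nothing beyond that. Programme-level sustainability is untouched, and the 6- and 12-month outcome analyses stand as end-of-phase and end-of-programme results.

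A reader might go further and infer that the 12-month effect overstates the lasting effect by some calculable factor. The documents do not support that. They give no regain rate, and the only effect size, 2.3 kg, is a planning value for the first six months and cannot stand in for the T3 effect. Neither the size nor the existence of later regain can be derived here; the trial simply will not observe it.

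The change is worth making because it alters what the trial can properly conclude.

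**What to change.** Four changes of wording, with no new data collection:

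1. In the Evaluation section and in reports, describe T3 outcomes as end-of-programme outcomes.
2. In Table 4, define the participant-level Maintenance indicator as *change from T2 to T3 under aftercare*. Keep the programme-level Maintenance items as they are.
3. In the abstract and in later conclusions, limit sustainability wording for clinical and behavioural outcomes to persistence under continued support, and distinguish it from sustainability of the programme in the health system.
4. In the limitations paragraph of the Discussion, add that no participant outcome is measured after aftercare ends.

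The direct cost is close to nil, since the T2 and T3 measurements are already planned. The real cost is a less favourable durability claim: the study could report that gains were, or were not, held with six months of aftercare, but not that they last without it.

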#### Quality control

Two different tools, proven effective during previous European projects are included to assure quality control. During the intervention, PDSA methodology [32], acronym of “plan, do, study and act” ensures to make corrections and fine-tune the design for future use. The second tool will be the Standards for Quality Improvement Reporting Excellence (SQUIRE) [33], which are a set of 19 descriptive units that present how to examine and develop quality improvements in healthcare. The guidelines were developed over the years to respond to the insufficient and limited studies published in this field. They have proven to be useful designing implementation, and for writing communications.

#### Transfer

The Consolidated Framework for Implementation Research (CFIR) [28] will be used to examine factors influencing different levels of care delivery (patient care, delivery groups, health organisation or policy) that could hinder or facilitated the implementation of the best practice in C4D. The CFIR offers some constructs that have proven effective during the implementation. It is adaptable to a variety of contexts and settings, and covers five key domains: the intervention, the internal and external environment, the people involved, and the implementation process itself. Each domain comprises multiple constructs that interact in complex ways to influence the effectiveness of implementation. CFIR provides the multidisciplinary teams with a specific methodology to identify relevant factors influencing implementation and increasing their potential success rate for future implementations.

## Discussion

C4D will be highly relevant to the EU 4 H Programme [34], which sets as one of their key priorities the decrease in the impact of non-communicable diseases on individuals and on society. Based on RD2N effective lifestyle treatment for people with T2DM and the underlying principles of behavioural change (I-Change model) [26], the C4D purpose will be to improve and foster health in the EU Member States by reducing the burden of T2DM and its related risk factors and complications, both at societal and personal level.

Adopting general healthier habits in life can have wide-reaching positive effects on various health parameters as they are interconnected, and positive changes in one area often contribute to improvements in others like cardiovascular, respiratory, and other non-communicable diseases: bone health, stronger immune and cognitive function. Although the concept of T2DM remission has emerged as a real-world option, effective implementation in routine clinical practice may not be feasible until long-term studies prove the efficacy of different approaches [35] and the different European context testing the Dutch RD2N practice will contribute to those efforts. The common peer groups will be a novel contribution to enhance diabetes knowledge, reinforce each other, and receive support for change in behaviour [4], adding mental and social well-being to the results.

Improved lifestyle, and risk factor management among people with T2DM may reduce costs related to T2DM treatment, and in the long term, costs related to reduced functional and working capacity [36] and to the management of T2DM complications. The diversity on the socioeconomic context, healthcare systems, and the level of commitment from the 12 countries participating demand tailored approaches to consider the unique characteristics and challenges of each one of them. It underscores the relevance of collecting data and insights from various sources to inform successful implementation strategies in different scenarios.

The absence of a control group in the study limits the ability to draw strong conclusions or causal claims about the effects of the intervention. These actions will test the feasibility and practical aspects of the intervention, and control groups should be introduced in subsequent studies once the C4D is over, for the purpose of attributeing observed changes or outcomes truly because the intervention and not to other factors that might influx.

The results of C4D are expected to support new EU policies, as all countries see their affected population increase and seek for a sustainable reduction in the overall burden of T2DM and its related risk factors and complications.

